## Statistical Analysis

### Safety Analysis

Adverse events will be tabulated by treatment group, severity and relation to treatment.

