***Study protocol***

After signing the informed consent, patients will be randomized in 1:1 manner into the treated or the control-cross group. After the randomization, patients will be invited for baseline evaluation that will include full review of their medical status and complete physical examination. All patients will present baseline anatomical scan (CT/MRI). After their inclusion, patients will be randomized to two groups: a treated group and a cross group. All patients will go through evaluation of their neurocognitive function using neurocognitive testing battery, quality of life using EQ-5D questionnaire and brain functional imaging (rCBF-SPECT scan). The patients in the treated group will be evaluated twice – at baseline and after 2 months of HBOT treatment. The patients of the cross group will be evaluated three times – at baseline, after a 2 month control period of no treatment and after a consequent 2 month period of HBOT treatment. We emphasize that the study will be a cross-over trial and patients in the cross group will receive HBOT treatment after their second evaluation and will go through a third neurological evaluation after the cross, when they will complete their HBOT.

The following HBOT treatment protocol will be practiced: The patients will go through 40 HBO treatments (each treatment session will be given on a separate day), distributed over two months (five days a week). Each session will be for 60 minutes in 100% oxygen atmosphere and at pressure of 1.5 ATA.

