**Study Files**

The medical records will be maintained adequately to enable good data storage and latter on management. Subjects' clinical source documents will include (but not limited to) the following: subject's hospital/clinic/ hyperbaric unit records, physician’s and nurse’s notes, appointment book, original laboratory reports, electroencephalogram (EEG), X-ray, SPECTs, CT and special assessment reports, consultant letters, screening and enrollment log, etc.

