**Statistical Considerations**

## Analysis Sets

### Safety Analysis Set

The safety analysis set will consist of all subjects with whom the study treatment was initiated.

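### Adverse-event recording is not equalised between the 40-session HBOT periods and the no-treatment control period, and the safety table is not split by period

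*Protocol*

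**What the plan says.** - **Aim.** Protocol, Objectives: the safety of HBOT in this population is to be evaluated and adverse events recorded.
- **Analysis.** Protocol, Safety Analysis: "Adverse events will be tabulated by treatment group, severity and relation to treatment". No rate, test, time window or split by study period is given.
- **Analysis set.** Protocol, Safety Analysis Set: "The safety analysis set will consist of all subjects with whom the study treatment was initiated".
- **Recording window.** Protocol, Adverse Events: new or worsened events count from the screening visit to the last study day. Control-period events are therefore included.
- **Contact under HBOT.** Protocol, Study protocol: "40 HBO treatments (each treatment session will be given on a separate day), distributed over two months (five days a week".
- **Contact in the control period.** Same section: "The patients of the cross group will be evaluated three times – at baseline, after a 2 month control period of no treatment". Nothing is listed between those two evaluations. Afterwards, "patients in the cross group will receive HBOT treatment after their second evaluation".
- **Content of evaluations.** Study protocol and Neurocognitive evaluation: cognitive battery, EQ-5D and SPECT. A medical review and physical examination are named at baseline only. An adverse-event enquiry is not named at month 2 or month 4.
- **Assessment of events.** Assessment of Adverse Events states how a known event is graded and attributed. It does not state when or how patients are asked.
- **Blinding.** Randomization: there is no placebo in the control period, and patients know their arm.

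**The concern.** How often a minor event is recorded depends partly on how often someone is there to hear about it. An HBOT patient meets chamber staff on 40 separate days, and the source documents listed under Study Files include "hyperbaric unit records, physician’s and nurse’s notes". A control-period patient has no listed encounter until month 2, and the protocol does not say that adverse events are asked about then.

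The untreated period is the trial's only internal guide to background events. The Background section lists headaches and sleep disorders among the sequelae of brain injury, and the relatedness rule asks whether an event is readily explained by the patient's clinical state. If control-period events are captured less completely, ordinary worsening of such symptoms can look like an effect of HBOT. Splitting a table at the analysis stage cannot recover events that were never elicited.

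**Working it through.** **Contact count.** 40 sessions / 5 per week = 8 weeks, which agrees with the stated two months. Contacts listed in the control period, after baseline: one, at month 2.

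**What has to be assumed.** The protocol gives no event rates and no detection probabilities. Let s_H and s_C be the shares of true events that are recorded in an HBOT period and a control period. Take the same true rate in both periods. Then:

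- HBOT period against control period (also treated against cross in months 0-2): recorded ratio = s_H / s_C.
- Whole study by randomised group: the treated group contributes s_H per patient over two months, and the cross group contributes s_C + s_H over four. The cross/treated ratio of counts per patient is (s_C + s_H) / s_H. Per month it is half of that.

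**Range A: detection assumed directly** (s_H 0.9 to 1.0)

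| s_C | HBOT / control period | Cross / treated, per patient | Cross / treated, per month |
|---|---|---|---|
| 0.3 | 3.0-3.3 | 1.30-1.33 | 0.65-0.67 |
| 0.5 | 1.8-2.0 | 1.50-1.56 | 0.75-0.78 |
| 0.7 | 1.3-1.4 | 1.70-1.78 | 0.85-0.89 |
| 0.9 | 1.0-1.1 | 1.90-2.00 | 0.95-1.00 |

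**Range B: detection from a forgetting model.** Events fall uniformly over the interval before the next contact, and the chance of reporting halves every h days. The mean share reported is (1 - e^(-kL)) / (kL), with k = ln 2 / h and L the length of the interval. For the control period L = 61 days. For HBOT L = 7/5 = 1.4 days, which treats every session as an occasion to report.

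| h (days) | s_C | s_H | HBOT / control period | Cross / treated, per patient | Cross / treated, per month |
|---|---|---|---|---|---|
| 7 | 0.165 | 0.934 | 5.7 | 1.18 | 0.59 |
| 14 | 0.315 | 0.966 | 3.1 | 1.33 | 0.66 |
| 28 | 0.516 | 0.983 | 1.9 | 1.52 | 0.76 |

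Worked line for h = 7: k = 0.0990. For the control period kL = 6.04 and s_C = (1 - 0.0024) / 6.04 = 0.165. For HBOT kL = 0.139 and s_H = 0.934. The ratio is 0.934 / 0.165 = 5.7. The cross group records 0.165 + 0.934 = 1.10 events for every 0.93 in the treated group.

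**Reading.** A period contrast is inflated by a factor between about 1.0 and 5.7, depending wholly on detection. A whole-study count by randomised group points the other way, because cross patients contribute two periods. Per month of follow-up, the cross group shows fewer events or the same. With s_H = s_C the period ratio is 1.0.

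**The case against.** A reader might infer that the plan compares event rates between HBOT and untreated controls, and that the excess on HBOT is built in. The protocol does not support that.

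- The Safety Analysis section plans a tabulation, with no rate comparison. *This stands*, although columns set side by side by group invite comparison without a test.
- The groups are treated and cross, and both receive HBOT. The safety set holds only patients who started treatment, so no never-treated group is tabulated. *This stands*, and it is why the direction of a table by group is not determined. The excess belongs to a period contrast that the protocol does not spell out.
- Control-period events fall inside the recording window and could be asked about at month 2. It would be wrong to say that controls have no scheduled contact, since an evaluation ends the period. *This stands*: the bias is likely, not certain.
- Pre-existing conditions that do not worsen are not adverse events, and the patients enrolled have stable complaints. *This stands in part*: it shrinks the pool of background events, but exacerbations and new events still count.
- The Study Files list is general and does not describe adverse-event collection, and nothing says that each session serves as an enquiry. *This stands*: the list is only supporting evidence, and Range B is an illustration.
- The analysis plan or case report form, neither of which is at hand, may settle elicitation and period splits. *This stands in part*: an analysis plan can split a table by period, but collection must be fixed before data are gathered. The protocol sets out its evaluations without an adverse-event enquiry.

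**Conclusion.** The point holds in a limited form. Contact is clearly unequal, the control is open without sham, and the protocol fixes neither a common enquiry nor a table by period. Any contrast of HBOT periods with control periods is likely to show more recorded events on HBOT at equal true rates. The inflation could be negligible (about 1.0 when s_C is 0.9) or large (5.7 with a seven-day reporting half-life). Every figure in that range rests on assumed detection, since the protocol supplies none.

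Two stronger conclusions do not follow: that the bias is certain, and that the planned table as worded must run against HBOT. Safety is a stated aim but neither a primary nor a secondary endpoint, so this is a minor and inexpensive improvement.

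**What to change.** In Safety Analysis, Adverse Events and Assessment of Adverse Events:

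1. Put the same structured adverse-event questions, covering the preceding two months, to every patient at each existing evaluation: month 2 in both groups and month 4 in the cross group.
2. Tabulate events by period (control or HBOT).
3. Base any months 0-2 contrast of treated with cross only on events obtained by this common enquiry.
4. Report events noted at chamber sessions in a separate HBOT-only table, so that nothing is lost from the HBOT safety record.

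The cost is one short form at visits that already take place and one more table. The drawback is under-recall of minor events in the contrast: under Range B a single two-month enquiry would capture about 17% to 52% of them. Equal enquiry also reduces the bias without removing it. Patients know their arm, and those who have already discussed an event at a session may recall it better. A sentence to that effect belongs with the table.

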**Randomization**

Since the diversity of the patients included in the study, after signing the informed consent is expected to be high, no stratifies criteria will be used. Patients will be randomized in 1:1 fashion to either treatment or controlled-cross group.

There will be no placebo in the cross group during the control period. The only way to give “placebo” of HBOT, is to bring the patients to the hyperbaric chamber and to increase the environmental pressure in a way the patients will “feel the hyperbaric pressure” in their ears. However, Henry’s law states: “the amount of a given gas dissolved in a given type and volume of liquid is directly proportional to the pressure of that gas in equilibrium with that liquid”. Thus, hyperbaric environment significantly increases the dissolved oxygen pressure even if a person holding his breath [[29](#_ENREF_29)]. Moreover, the alternative of hosting the patients in the hyperbaric chamber without any pressure increase cannot serve as a real placebo since the patients will not feel the pressure. Accordingly, the only real “placebo” could be achieved by increasing the pressure and reducing the percentages of the oxygen but that holds significant safety consideration.

From the ethical point of view, it is deemed unethical to “treat” the patients (40 sessions in the hyperbaric chamber) while they actually know that it is a placebo. In order to somewhat compensate for this limitation, the control will be a cross group and after the 2^nd^ evaluation at the end of a control period they will be crossed to HBOT. The cross for treatment enables intra-group efficacy evaluation in both treatment and control group.

Since the patients will know they are not receiving HBOT during the control period they will not be blinded with regard to the treatment arm. Accordingly, the quality of life evaluations will not be blinded. However, the complete blindness evaluation can be assured in both of the primary end points of this study, The Mindstreams computerized evaluation and the brain SPECT evaluation done by the radiologist.

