**Adverse Events**

An adverse event (AE) is any untoward medical occurrence in a clinical investigation subject administered a medicinal product and which does not necessarily have a causal relationship with this treatment. An AE can therefore be any unfavorable and unintended sign, symptom, or disease temporally associated with the use of a medicinal product, whether or not considered related to the medicinal product. Pre-existing events, which increase in severity or change in nature during or as a consequence of use of a medicinal product in human clinical trials, will also be considered AEs.

Any medical condition or clinically significant laboratory abnormality with an onset date before the screening visit and not related to study procedures is considered to be pre-existing, and should be documented in the case report form.

Any AE (i.e., a new event or an exacerbation of a pre-existing condition) with an onset date after the screening visit up to the last day on study (including the follow-up, off study medication period of the study), should be recorded as an AE on the appropriate CRF page(s).

An AE does not include:

- Medical or surgical procedures (e.g. surgery, Endoscopy, tooth extraction, transfusion); the condition that leads to the procedure are an adverse event.
- Pre-existing diseases or conditions or laboratory abnormalities present or detected prior to the screening visit that does not worsen.
- Situations where an untoward medical occurrence has not occurred (e.g. hospitalization for elective surgery, social and/or convenience admissions).
- Overdose of either study drug or concomitant medication without any signs or symptoms unless the subject is hospitalized for observation.

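### Adverse events tabulated by randomised group set 2 HBOT months against 2 untreated plus 2 HBOT months, so the all-cause table cannot show HBOT against no treatment

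*Protocol*

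**What the plan says.** The Safety Analysis section of the protocol gives one rule: "Adverse events will be tabulated by treatment group, severity and relation to treatment". It mentions neither study period nor treatment at the time of onset.

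The Safety Analysis Set section says: "The safety analysis set will consist of all subjects with whom the study treatment was initiated". Study treatment is not defined there.

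Under Study protocol, the treated group is evaluated "at baseline and after 2 months of HBOT treatment". The cross group is evaluated at baseline, "after a 2 month control period of no treatment and after a consequent 2 month period of HBOT treatment". The same section states that "patients in the cross group will receive HBOT treatment after their second evaluation", so HBOT is planned for all of them.

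The Randomization section says: "Patients will be randomized in 1:1 fashion to either treatment or controlled-cross group". It adds: "The cross for treatment enables intra-group efficacy evaluation in both treatment and control group". Treatment group and control group there name the randomised arms.

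The Adverse Events section asks for any event "with an onset date after the screening visit up to the last day on study" to be recorded, and the assessment section that follows requires the onset date. The Objectives name the safety of HBOT in this population as something to be evaluated.

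**The concern.** In a one-way crossover of this kind, the randomised arm does not identify exposure after the second evaluation. A table by arm over the whole study puts HBOT-period events of crossed patients into the column a reader takes as the control. It also gives that column twice the observation time.

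The only concurrent untreated information in the trial is the cross group's first two months. It is the background against which all-cause events on HBOT could be judged, and the stated table does not isolate it. The protocol uses the crossover structure for its within-group efficacy evaluation but not for safety. At stake is whether the one planned safety table can serve the stated safety aim. The primary analysis, sample size and success rule are not affected.

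**Working it through.** **No figure to reproduce.** The protocol states no adverse event rate and no safety power, so the check is a reading of the text plus an illustration under assumed rates.

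**Exposure in each column, from the protocol**

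| Column | Untreated months | HBOT months | Total |
|---|---|---|---|
| Treated group | 0 | 2 | 2 |
| Cross group | 2 | 2 | 4 |

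**Assumed inputs.** b is the probability of at least one background event in 2 months, taken as 5-20%. h is the probability of an HBOT-caused event during one course, taken as 5-30%. Events are independent across periods and sources, b is the same in both periods, and all cross patients complete both periods.

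**Formulas for the proportion with at least one event**

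- Treated group: 1 - (1-b)(1-h)
- Cross group, control period only: b
- Cross group, whole study: 1 - (1-b)²(1-h)
- Table by arm, treated minus cross: (1-b)²(1-h) - (1-b)(1-h) = -b(1-b)(1-h)
- By treatment at onset, treated months 0-2 minus cross months 0-2: 1 - (1-b)(1-h) - b = (1-b)h

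The by-arm difference is never positive, whatever h is. The contrast by treatment at onset is positive whenever h is above zero and b is below one.

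**Results (percent; differences in percentage points)**

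| b | h | Treated | Cross, control period | Cross, whole study | Difference by arm | Difference by treatment at onset |
|---|---|---|---|---|---|---|
| 5 | 30 | 33.5 | 5 | 36.8 | -3.3 | +28.5 |
| 10 | 20 | 28.0 | 10 | 35.2 | -7.2 | +18.0 |
| 20 | 5 | 24.0 | 20 | 39.2 | -15.2 | +4.0 |
| 20 | 30 | 44.0 | 20 | 55.2 | -11.2 | +24.0 |

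The first and third rows give the extremes of both differences over the assumed range. In the second row, for example, the cross group's whole-study figure is 1 - 0.9² × 0.8 = 0.352 and the treated figure is 1 - 0.9 × 0.8 = 0.28.

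**Does dividing by time repair the table?** Only in part. Read b and h as expected events per patient. The treated rate is (b+h)/2 per person-month, the whole-study cross rate is (2b+h)/4, and the control-period rate is b/2. With b = 0.10 and h = 0.20 these are 0.150, 0.100 and 0.050. The by-arm rate difference is 0.150 - 0.100 = 0.050, half of the 0.150 - 0.050 = 0.100 seen by treatment at onset.

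**Does the relatedness split repair it?** Not as a comparison. Both arms receive one course of HBOT, so both have the same expected proportion h with an HBOT-caused event, and the arm difference is zero.

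**Safety set.** If study treatment means HBOT, a cross patient enters the set only by starting HBOT. One who leaves during the control period is excluded, and so are that patient's untreated-period events. The protocol states no expected drop-out, so this effect cannot be sized.

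**The case against.** The safety rule is a single sentence, and a statistical analysis plan that is not shown may add the detail. Treatment group is not defined where it is used, and it could be specified as treatment at onset or shown with a split by period. That much stands, and it limits how firmly the point can be put. It does not remove the point: the protocol states a tabulation rule and a safety set, and its own use of the group names points to the randomised arms. Even a period split would leave the safety set to be settled.

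A reader might infer that HBOT harms would be hidden. The documents do not support that. The same sentence tabulates by relation to treatment, and a Yes rating requires a temporal link to the study drug or study procedures, so related events would appear in either column. What remains is narrower. Relatedness is an investigator's judgement in a trial where patients know their assignment, and no blinding of adverse event assessment is described. It cannot replace a concurrent untreated rate for all-cause events.

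A reader might also infer that a planned safety comparison is lost. The protocol promises none: it plans a tabulation, with no safety hypothesis or test. Nor are data lost. Onset dates are recorded, so the first two months of both arms can still be compared.

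Finally, restricting a safety set to patients who started treatment is a usual way to describe the safety of a treatment. That is fair for the HBOT columns, but not for an untreated reference column.

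**Conclusion.** The point holds in a limited form. Taken as written, with treatment group meaning randomised arm, the all-cause table compares 2 HBOT months with 2 untreated plus 2 HBOT months and cannot show HBOT against no treatment. Under the simple model, the by-arm difference in patients with an event is zero or negative however harmful HBOT is: -3.3 to -15.2 points over the assumed range, against +4 to +28.5 by treatment at onset.

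These sizes rest entirely on assumed rates, on independence and on full follow-up in both arms. They show the direction of the distortion, not its expected size in this trial. The adverse event section also mentions an off-medication follow-up that the visit schedule does not describe. The table of exposure assumes it adds no time that differs between the arms.

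The safety set part is conditional on study treatment meaning HBOT and on some cross patients leaving before HBOT. The documents do not establish that any will. The point deserves correction before the safety tables are produced.

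**What to change.** Tabulate adverse events by treatment at onset, in three columns:

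- (a) treated group, HBOT, months 0-2
- (b) cross group, control period, months 0-2
- (c) cross group, HBOT, months 2-4

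Give the number of patients and the exposure time as denominators for each. Use (a) against (b) as the randomised contrast, and pool (a) and (c) to describe all HBOT exposure. Keep severity and relatedness as further breakdowns.

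Define study treatment in the safety set, and keep in the set, for column (b), every cross-group patient who entered the control period, whether or not HBOT was later started.

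The cost is somewhat more tabulation and a short rewording of the safety set definition. No new data are needed, because onset dates are already collected.

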### Primary Efficacy Analysis

For the primary end point, Neurocognitive function (using Mindstreams neurocognitive battery test score), we will compute Overall Proportion of Success:

The following hypotheses are specified and will be tested separately:

For Neurocognitive *tests score* proportion of improvement:

H_0_: p_1=_ p _2_

H_1_: p_1>_ p_2_

While p1= Neurocognitive function (using Mindstreams neurocognitive battery *tests score*) improvement as a result of the HBOT training (assumed to be 0.12); and

p2= Neurocognitive function (using Mindstreams neurocognitive battery *tests score*) improvement as a result of test-retest effect (assumed to be 0.02)

This hypothesis will be tested by:

1. Constructing a one-sided, lower 95% confidence interval about the observed Overall Proportion of Success in the relevant cohort.
2. Examining whether the lower limit of the confidence interval is at or above the success criterion

Study success will be declared if the following is met:

1. Lower confidence limit of HBOT treatment success is at 0.12 or above

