***End-point evaluation***

**Neurocognitive evaluation**

The neurocognitive evaluation will be done at baseline and after 2 months for all patients. In the cross group a 3^rd^ evaluation will be performed after 4 month- after crossing and completing 2 months of HBOT treatment. Cognitive function will be assessed using the one-hour Mindstreams Computerized Cognitive Test Battery (Mindstreams; NeuroTrax Corp., NY). Detailed description of the tests can be found on Neurotrax website ([www.neurotrax.com](http://www.neurotrax.com)).

To minimize differences in age and education, each outcome parameter will be normalized and fit to an IQ-like scale (mean=100, S.D=15) according to patient's age and education. Normalized subsets of outcome parameters will be aggregated to produce four index scores relevant to mild TBI: **Memory, Attention, Executive function,** and **Information Processing Speed**.

Three different test versions exist in the Mindstreams testing battery to allow repeated administrations, test-retest reliability for those versions were evaluated and found high, with no significant learning effect [[23](#_ENREF_23),[24](#_ENREF_24)].

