**Sample Size Considerations**

Presentation of sample size is based on achieving 80% power overall to demonstrate that improvement rate in *mindstreams score* is at least 12%. An improvement rate of at least 10% in the neurocognitive score in treatment group (compared to baseline, prior to HBOT treatment) would be an appropriate clinical target for HBOT treatment success and of sufficient interest to encourage further investigation of HBOT treatment for post TBI patients suffering chronic neurocognitive deficiencies.

Sample size is based on the assumption that exposure to the *mindstreams* tests at baseline without any additional training might induce 2% score improvement in the second test, following treatment, (test-retest effect). Assuming a true success rate of 12% a sample of N = 31 will provide 80% power to show that HBOT treatment induces at least 10% improvement on *neurocognitive test score*. This is based on a power analysis using the normal approximation for the binomial, with one-sided Alpha=0.05.

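### The primary analysis and sample size use 0.12 and 0.02 both as sizes of a score change and as shares of patients, so N = 31 and its 80% power do not apply to the stated effect

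*Protocol*

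**What the plan says.** **The outcome is continuous.** Under *Neurocognitive evaluation*, "each outcome parameter will be normalized and fit to an IQ-like scale (mean=100, S.D=15") according to age and education. Subsets of these are then aggregated into "four index scores relevant to mild TBI".

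**The effect is a size of change.** *Sample Size Considerations* says that prior exposure to the test "might induce 2% score improvement in the second test". It sets the clinical target as "An improvement rate of at least 10% in the neurocognitive score in treatment group (compared to baseline, prior to HBOT treatment").

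**The same figures then become a proportion.** The same section goes on to call the 12% a true success rate and says of N = 31 and 80% power: "This is based on a power analysis using the normal approximation for the binomial, with one-sided Alpha=0.05".

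**The test combines both.** *Primary Efficacy Analysis* defines p1 as Mindstreams "improvement as a result of the HBOT training (assumed to be 0.12") and p2 as "improvement as a result of test-retest effect (assumed to be 0.02"). Yet the statistic is a proportion ("we will compute Overall Proportion of Success"), judged by a one-sided lower 95% confidence limit.

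**The concern.** A mean percentage gain in a score and the percentage of patients who succeed share a unit sign and nothing else. The first needs an SD of change. The second needs a rule that makes a patient a success, and its variance then follows from the proportion. The protocol takes its numbers from the first and its variance formula from the second. It gives no SD of change and no per-patient rule.

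At stake are the primary test and the basis for the trial's size. An analyst following *Primary Efficacy Analysis* must either put a binomial interval around a mean change, where it does not belong, or supply a cut-off for which 0.12 and 0.02 were not derived. In both cases the planned power describes a different quantity from the one analysed.

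**Working it through.** **Inputs from the protocol.** p2 = 0.02, p1 = 0.12, power 80%, one-sided alpha 0.05, N = 31 (*Sample Size Considerations*, *Primary Efficacy Analysis*); score scale with mean 100 and SD 15 (*Neurocognitive evaluation*).

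**Assumptions, because the protocol gives no figure.** SD of change 10 to 15 points (20 as an upper case for sizing); normally distributed change; baseline near 100, so that 1% is about 1 point. If the between-patient SD is 15 at both visits, the SD of change is 15·√(2(1−r)): 15.0 at r = 0.5, 11.6 at r = 0.7 and 9.5 at r = 0.8.

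**Step 1: reproduce N = 31.** The single-proportion formula is

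n = [z_α·√(p2(1−p2)) + z_β·√(p1(1−p1))]² / (p1−p2)²

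with √(0.02·0.98) = 0.140, √(0.12·0.88) = 0.325 and z_β = 0.842.

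- z_α = 1.96: [0.2744 + 0.2735]² / 0.01 = 30.02, rounded up to **31**.
- z_α = 1.645, the stated one-sided 0.05: [0.2303 + 0.2735]² / 0.01 = 25.4, rounded up to 26.

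The stated figure comes out when the two percentage changes are entered as shares of patients, though with the two-sided critical value. Other binomial variants at one-sided 0.05 give different answers (35 with a continuity correction, the arcsine method or the exact test). The per-patient SDs behind N = 31 are therefore 0.140 and 0.325. Neither is linked to the spread of a change on a scale with SD 15.

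**Step 2: are the two quantities interchangeable?** The share of patients gaining at least 10% is Φ((mean − 10)/SD).

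| Mean change | SD 10 | SD 15 | Share used in the protocol |
|---|---|---|---|
| 12% | Φ(0.20) = 58% | Φ(0.13) = 55% | 12% |
| 2% | Φ(−0.80) = 21% | Φ(−0.53) = 30% | 2% |

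Under these assumptions a 10% threshold cannot make 0.12 and 0.02 serve as both mean changes and responder shares.

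**Step 3: the interval.** The binomial SE at 0.12 with n = 31 is √(0.12·0.88/31) = 5.8 percentage points. The SE of a mean change is 9.5/√31 = 1.7 points to 15/√31 = 2.7 points for SDs of 9.5 to 15. The ratio is 2.2 to 3.4. It depends on the assumed SDs and compares like with like only near a baseline of 100. In this range the binomial interval is too wide, so the error is on the conservative side.

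**Step 4: size on the stated effect.** 12% minus 2% is 10 points at a baseline near 100. For a two-arm t-test on change, one-sided 0.05, 80% power:

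| SD of change | n per arm |
|---|---|
| 10 | 14 |
| 15 | 29 |
| 20 | 51 |

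Read the other way, 31 per arm gives 80% power at an SD of change of about 16. A single group of 31 against a fixed 2% does so at about 22. The protocol does not say whether 31 is per arm or in total.

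**The case against.** The best defence is a responder reading: success means a patient who gains at least 10%, with 12% of patients succeeding on HBOT and 2% on retesting. A binomial calculation would then be coherent, and the threshold could sit in an analysis plan that is not shown. It is fair that the absence of a threshold here does not prove that none exists. But the text does not read this way. The 2% is called a score improvement, and p1 and p2 are both defined as improvement in the test score. The fault is that one stated number is given two meanings, and a threshold supplied elsewhere would not remove that. Nor would the reading support N = 31 for the randomised comparison: 12% against 2% needs 80 per arm at one-sided 0.05, and 31 per arm gives about 46% power.

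Three stronger readings are tempting and are not supported.

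- **The trial is too small.** A reader might infer this, but the direction depends on an SD of change that the protocol does not give. 31 per arm would be ample at SD 10 and short at SD 20.
- **Four index scores are each tested at 5%.** *Primary Efficacy Analysis* speaks of hypotheses tested separately, but one hypothesis follows, on the test score. Nothing says that the four indices are tested one by one. What stands is that four indices exist and the score to be tested is not identified among them.
- **A responder cut-off would lose most of the power.** It would lose some. Assume mean 90, SD 15, r = 0.7, a true 9-point effect and 31 per arm. A 10% cut-off then gives about 72% power, against about 92% for the continuous change.

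**Conclusion.** The point holds. *Sample Size Considerations* and *Primary Efficacy Analysis* use 0.12 and 0.02 both as sizes of a score change and as binomial proportions. The conflict can be read directly from the text and needs no assumed figure. The reproduction of N = 31 shows that it reached the sample size. The stated 80% power therefore does not apply to the stated effect, and the planned confidence limit uses the wrong variance.

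The size of the mismatch is illustrative. The shares of 55-58% and 21-30% rest on an assumed SD of change of 10 to 15 points, normality and a baseline near 100. The protocol does not allow a conclusion on whether N should be larger or smaller. Because this concerns the primary endpoint, its test and its sample size, it should be corrected before the analysis.

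**What to change.** 1. In *Primary Efficacy Analysis*, replace the binomial proportion and its confidence limit with a continuous analysis of one pre-named Mindstreams score at month 2. Compare the randomised HBOT and control groups by ANCOVA with the baseline score as covariate.
2. State the target as a between-group difference in points. The sponsor's 12% minus 2% is about 10 points at a baseline near 100. It is less at a lower baseline (9 points at 90), so the expected baseline should be stated too.
3. In *Sample Size Considerations*, restate N and power with an assumed SD of change and its source, and say whether N is per arm or total. The per-arm figures in Step 4 show the range. They are for a t-test on change, so ANCOVA should need no more.
4. If a responder share is preferred, state the per-patient threshold, use responder rates that agree with it in both groups, and size the trial on those rates.

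Cost: no new data are collected, but this is more than a change of wording, because the stated N or power may change. If the named score is a composite of the four indices, it can dilute an effect confined to one domain.
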